### Subgroup analyses

We expect that general practices will implement named accountable general
practitioners in various ways and that the effectiveness of the intervention may
depend on factors related to the local context in which the general practices
operate [25]. Therefore, we will
characterise general practices according to: setting (urban/rural, based on the
RUC2011 classification at small area level) [44], average socioeconomic deprivation score of their patients,
number of general practitioners within the practice and practice list size. We
will also include the average number of patients per full-time equivalent
general practitioner. We will estimate treatment effects separately for each
general practice and then test the relationship between these treatment effects
and general practice characteristics using a practice-level, linear regression
model [45].

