## Methods

### Reform to the general medical services contract in England

The 2014/15 General Medical Services contract introduced a requirement for
general practices in England to offer patients aged 75 or over a named
accountable general practitioner, who should provide longitudinal continuity of
care within the general practice and be accountable for coordinating care to
meet the patient’s health and social care needs. In particular, the named
accountable general practitioner should ensure that patients receive all
appropriate services and work with relevant associated healthcare and social
care professionals to deliver a multidisciplinary care package [24,35]. The contract requires that the practice notify the patient of their
named accountable general practitioner, usually by letter, and make a reasonable
effort to accommodate patient preferences about the choice of general
practitioner. However, patients are not prevented from seeing any other general
practitioner in the practice [36]. The
2014/15 GMS contract changes led to a step change (discontinuity) in the
percentage of patients receiving a named accountable general practitioner, which
increases from around 5% to around 80% near age 75 (Table 1).

**Table 1 T1:** Preliminary analysis of data from Clinical Practice Research Datalink
showing that the requisite discontinuity exists in the data.

	Patients aged 70–74 (%)	Patients aged 75–79(%)

Notified of named accountable general practitioner	5420 (5%)	67,770 (80%)
Not notified of named accountable general practitioner	99,830 (95%)	17,161 (20%)
Total	105,250	84,931

*Note:* Based on preliminary analysis of Clinical
Practice Research Datalink data. Figures are illustrative as this
analysis was based on 2014 data and not all exclusion criteria were
applied.

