### Study cohorts

All general practices in England were mandated to participate in the policy. We
will examine data from the electronic medical record of a national sample of
general practices that participate in the UK-wide Clinical Practice Research
Datalink. This is a validated and widely used research database that contains
anonymised, person-level clinical data for all registered patients, linkable to
other data sources, such as death records from the Office for National
Statistics and Hospital Episode Statistics administrative data [38].

We will study all English general practices that have submitted data to Clinical
Practice Research Datalink for the full 2014/15 financial year, excluding
practices for which data are identified by Clinical Practice Research Datalink
as not being up to research standard or that did not give permission for data
linkage. This is expected to result in approximately 200 practices. Within these
practices, we will study registered patients born between 1929 and 1949, and
thus aged between 65 and 85 in 2014. Patients will be excluded if they have
missing year of birth or gender, deregistered within the study period or were
identified as at high risk and started admission avoidance care, as part of the
Avoiding Unplanned Admissions Enhanced Service. All patients on the Service
received named accountable general practitioners irrespective of their age,
meaning that a regression discontinuity design is not appropriate for these
patients.

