## Statistical methods

Our initial analysis (Table 1) suggests that
the proportion of patients receiving a named accountable general practitioner is
discontinuous at the threshold, but this will be confirmed on receipt of the data.
We will also confirm that, although we would expect a trend in certain covariates
across age, there are no discontinuities in these covariates at age 75. This
comparison will be done graphically and include all patients, regardless of actual
treatment assignment. We do not expect such discontinuities to occur, but if they do
exist, this would lead us to question the validity of our study design.

As mentioned previously, the proportion of patients receiving a named accountable
general practitioner is unlikely to jump from 0 to 100% at age 75. It will therefore
be appropriate to apply a fuzzy regression discontinuity design [31], by fitting four regression models. Two
models will relate the outcome to a polynomial function of age: one model will be
fitted for people whose age lies within the bandwidth below the threshold and the
other model for people within the bandwidth above the threshold. The final two
models have treatment assignment as their dependent variable rather than outcome.
All models will use ordinary least squares regression and include patients
irrespective of their actual treatment assignment. We will calculate the estimated
treatment effect as the difference between the predictions of the two outcome models
at age 75, divided by the difference between the predictions of the two treatment
models at age 75.

The analysis will have regard to the rounded nature of the running variable (i.e.
age), resulting from the use of year of birth rather than full date of birth. This
will exclude the use of very small bandwidths, and so we will use a larger interval
spanning several years and model any trend in the endpoints by age using parametric
approaches based on polynomial functions [42,43]. In the absence of
information on full date of birth, it will not be possible to establish for a given
patient born in 1939 what date they turned 75, and therefore which side of the
threshold the patient is at the index date. We will remove the risk of
misclassification by excluding all patients born in 1939 when fitting the regression
models and making a small extrapolation around age 75 [42]. A final consideration is that, when the running variable
is only observed at discrete points, discretisation bias can occur because a change

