Moreover, where interventions are implemented haphazardly or with limited
fidelity to the intervention design, this might reduce the power of the study,
underscoring the need to assume conservative effect sizes when estimating the
required sample size.

Finally, many previous studies of integrated care interventions have used study
designs that are susceptible to con-founding arising from differences in
unobserved or observed patient characteristics [21,28]. In the current study,
the use of a regression discontinuity design will largely avoid these
concerns.

One limitation of this study is that the lack of full information on date of
birth means that our estimates are dependent on model specification [33], though we will test the sensitivity of
our findings. Also, the estimated treatment effects will only apply to
individuals aged close to 75 years, while younger or older groups might see
larger or smaller treatment effects. Our findings will also apply to the subset
of patients who are compliers and are not in the top 2% risk category. By
excluding the 2% of the population most at risk, we are omitting some of the
patients most in need of integrated care. However, a more intensive intervention
is currently being targeted at this group [54], and this intervention needs to be evaluated as a separate
study, something we might do at a later stage.

This study will examine four endpoints that could plausibly be affected by named
accountable general practitioners, namely general practitioner contact rates,
longitudinal continuity of care, referrals to specialist care and numbers of
diagnostic tests. It is possible that improvements in these endpoints may take
longer than 6 months to materialise but, to the extent that this is due to poor
implementation, the subgroup analysis may be informative. Moreover, while the
study will examine longitudinal continuity of care, it will not examine other
aspects of continuity, such as informational or management continuity [12,13], nor the patient experience of care.

We cannot determine whether the particular general practitioner contacts,
diagnostic tests and referrals to specialist care were appropriate. Although
continuity of care indices have been successfully applied to Clinical Practice
Research Datalink data in the past [20],
difficulties in analysing longitudinal data have been highlighted [12]. For example, although a staff
identifier is entered onto the computer system, practices may use shared login

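### Regressing about 200 practice-level fuzzy ratios on practice characteristics loses precision, and the slope becomes unstable if some practices have small treatment jumps

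*Protocol article*

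**What the plan says.** The Statistical methods section defines the effect as a ratio. The numerator is worded as "treatment effect as the difference between the predictions of the two outcome models". The denominator comes from the pair of models for receipt, in the words "at age 75, divided by the difference between the predictions of the two treatment". It is therefore the jump in recorded receipt of a named general practitioner.

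The Subgroup analyses section applies this practice by practice: "We will estimate treatment effects separately for each". A test relating the effects to practice features follows ("general practice and then test the relationship between these treatment effects"). The method for this second step is given as "and general practice characteristics using a practice-level, linear regression". The features are setting, deprivation, number of general practitioners, list size and patients per full-time equivalent general practitioner. On the number of practices, Study cohorts says: "This is expected to result in approximately 200 practices".

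For the sample as a whole, Table 1 is summarised by saying that receipt "increases from around 5% to around 80% near age 75". No figure is given for how receipt varies between practices, although the Subgroup analyses section expects implementation to vary. The last paragraph of the Introduction makes the link to practice characteristics part of the study's aim. Strengths and limitations, on benefit that is slow to appear because the policy was poorly carried out, adds: "implementation, the subgroup analysis may be informative".

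**The concern.** A ratio with a small, estimated denominator is very noisy and can take extreme values of either sign. Entering about 200 such ratios with equal weight in a linear regression lets the practices with the smallest jumps decide the slope. The check for a treatment discontinuity is not described practice by practice, so nothing in the text would catch this.

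The test could then have little power for a stated aim, and a null result could be read as evidence that the policy worked alike everywhere. Strengths and limitations itself criticises underpowered studies for that ambiguity.

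A second problem concerns what the ratios can show. Dividing by the treatment jump removes differences in uptake. Low uptake is the most direct form of poor implementation, and these ratios cannot reveal it. They may still reflect poor delivery among patients who were notified.

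**Working it through.** The article gives no power figure for the subgroup analysis. The one figure to reproduce is the average jump.

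**1. Average jump (Table 1).** 67,770/84,931 − 5,420/105,250 = 0.7979 − 0.0515 = 0.7464, or about 0.75. This agrees with the article's 5% to 80%.

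**2. Patients per practice.** Assume that the illustrative Table 1 counts come from 200 practices. Per year of age this gives 105,250/(5 × 200) = 105.25 below 75 and 84,931/(5 × 200) = 84.9 above.

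**3. SE of one practice's outcome jump.** The SD is 6 (Required sample size). Use linear fits, leave out age 75 and extrapolate to it. For each side the variance is (36/n per year) × (1/k + d²/Sxx), where k is the number of ages, d the distance of their mean from 75, and Sxx their sum of squares.
- Ages 70-74: 1/5 + 9/10 = 1.1. Ages 76-79: 1/4 + 6.25/5 = 1.5. SE = √[36 × (1.1/105.25 + 1.5/84.9)] = 1.006.
- Ages 65-74 and 76-85: 1/10 + 30.25/82.5 = 0.467 on each side. SE = √[36 × 0.467 × (1/105.25 + 1/84.9)] = 0.598.

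**4. SE of one practice's ratio.** Divide by the jump, treated for now as known.

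| True jump | Ages 70-79 | Ages 65-85 |
|---|---|---|
| 0.75 | 1.34 | 0.80 |
| 0.3 | 3.4 | 2.0 |
| 0.1 | 10 | 6.0 |
| 0.05 | 20 | 12 |

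The jump is itself estimated. With 5% receipt below 75 and 10% above, its SE on ages 70-79 is √(0.05 × 0.95 × 1.1/105.25 + 0.10 × 0.90 × 1.5/84.9) = 0.046. A true jump of 0.05 is then about one SE from zero, so the denominator can be near zero or negative.

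**5. Slope when every jump is 0.75.** With 200 equal-sized practices the SE is 1.34/√200 = 0.095 per SD of the characteristic. With unequal sizes (lognormal, assumed coefficient of variation 0.5) simulation gives 0.107 for the unweighted regression of ratios and 0.094 for a pooled model. For an assumed slope of 0.25:
- Ages 70-79: Φ(0.25/0.107 − 1.96) = Φ(0.38) = 65%, against Φ(0.25/0.094 − 1.96) = Φ(0.70) = 76%.
- Ages 65-85, with SEs 0.067 and 0.060: Φ(1.77) = 96%, against Φ(2.21) = 99%.

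The loss here comes from giving small and large practices equal weight.

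**6. Slope when uptake varies.** Simulated power uses mean uptake 80% above 75 and 5% below, linear fits, lognormal practice sizes and moderation of 0.25 contacts per SD. The SD of uptake is assumed; its ceiling at mean 0.8 is √(0.8 × 0.2) = 0.40.

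| SD of uptake | 70-79, ratios v pooled | 65-85, ratios v pooled |
|---|---|---|
| 0 | 64% v 76% | 97% v 99% |
| 0.1 | 60% v 73% | ratios 92-97% (SD up to 0.15) |
| 0.2 | 27% v 74% | 64% v 99% |
| 0.3 | 7% v 73% | about 7% v 99% |

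A repeat on ages 70-79 gave 31% v 76% at SD 0.2 and 5% v 79% at SD 0.3, so the figures are good to a few points. A different pattern, with 10% of practices at jump 0.05 and the rest at 0.83, gave 7% v 77% on 70-79 and 9% v 100% on 65-85. The median largest practice ratio there was about 235 and 100 contacts respectively.

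**7. Type I error.** With a true slope of zero, the regression of ratios rejected in about 4-6% of runs in every scenario.

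**The case against.** The strongest reply is that the damage is conditional. All English practices were mandated to take part, the average jump is large, and the article expects the vast majority of eligible patients to be covered by September 2014. Varied implementation may mean how the role was delivered, not whether the code was recorded. An uptake SD of 0.3 is an extreme choice: the Beta distribution used is U-shaped and puts about 5.5% of practices, or 11 of 200, at or below 10% uptake. The plan also rules out very small bandwidths and holds ages 65-85, where the stated method does well under modest spread. All of this stands, and it limits the size of the point.

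A second reply is that the cited method or a fuller plan may contain weights or a minimum-jump rule. That is possible. It does not remove the point, because the text fixes a ratio per practice followed by a linear regression, and a pooled model did better in every scenario examined.

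Three stronger readings are tempting, and the documents do not support them.
- That the subgroup aim cannot be answered: this needs a spread of uptake that the documents do not report.
- That the test will produce false positive slopes: rejection under no moderation stayed near 5%.
- That an SE of 1.34 against 0.25 shows failure: no single practice is tested, and 0.25 (5% of 5 contacts) is the article's main-effect target. It sets no target for moderation.

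**Conclusion.** The point holds in conditional form and should be fixed; it is not fatal. The subgroup method as stated is less precise than a pooled model even with equal jumps: about 64% v 76% power on ages 70-79 and 97% v 99% on 65-85. With uptake SD 0.2 it falls to about 27% and 64% on the two ranges. At 0.3 it has almost no power on either, while the pooled model keeps 73% and 99%. The consequence is lost power and an unstable slope.

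The remark about poor implementation in Strengths and limitations needs narrowing: the ratios cannot show low uptake, though they may show poor delivery among notified patients.

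These figures rest on assumptions: Table 1 counts spread over 200 practices, the same density extended to 65-85, linear fits, unequal practice sizes, an unweighted second stage, moderation of 0.25 contacts per SD and the uptake distributions shown. Quadratic fits would raise the single-practice SE at jump 0.75 to about 2.9 (70-79) or 1.4 (65-85).

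**What to change.** Replace the regression of practice ratios with one pooled two-stage least squares model. Treatment and treatment × characteristic are instrumented by eligibility and eligibility × characteristic. Include the characteristic's main effect, let the age trends vary by characteristic, and cluster standard errors by practice.

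Report the treatment jump by the same characteristics as the measure of implementation, and reword the remark in Strengths and limitations to match.

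A precision-weighted regression of the practices' outcome jumps can be added as a secondary analysis. It must be labelled as an effect of eligibility (intention to treat), because it does not estimate the complier effect that the article targets.

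The cost is different model code on the same data and about one paragraph of text. The trade-off to state is that the pooled estimate gives more weight to practices with larger jumps.

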### Required sample size

We believe that a 5% change in the number of general practice contacts would
represent a meaningful difference to general practice workload, since this
represents approximately one extra appointment per working day for an average
general practitioner [46]. Assuming an
average of 5 general practitioner contacts per 6-month period in the absence of
a named accountable general practitioner [47], and a standard deviation of 6 contacts [47,48], we will need
24,212 patients in each treatment group, at 90% power and two-sided p-value of

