0.05. Although the precise statistical power of the study will depend on the
bandwidth, the Clinical Practice Research Datalink database will provide more
than the required number of patients (Table 1) [37].

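### The stated 24,212 patients per group is twice what the plan's own inputs give; it equals the two-group total and appears to have been mislabelled

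*Protocol article*

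**What the plan says.** The section Required sample size in the protocol article gives every input to a two-group comparison of means:

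- **Target effect:** "We believe that a 5% change in the number of general practice contacts would" matter for practice workload.
- **Control mean:** an "average of 5 general practitioner contacts per 6-month period in the absence of" a named general practitioner.
- **Spread:** "a standard deviation of 6 contacts".
- **Result:** "24,212 patients in each treatment group, at 90% power and two-sided p-value of" 0.05.

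It states no allowance for the fuzzy design, the polynomial fit, clustering by practice or attrition. The only qualification is "0.05. Although the precise statistical power of the study will depend on the" bandwidth. The section then says that the database will supply more patients than are needed, and refers to Table 1. That table shows 105,250 patients aged 70–74 and 84,931 aged 75–79, and its note calls the figures illustrative.

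**The concern.** The article prints both the inputs and the answer, and the two disagree. This is therefore a misstated figure. It is not a detail left to a fuller document.

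A reader who checks the sentence gets half the printed number. A reader who trusts it may take the unexplained factor of 2 for an allowance for the regression discontinuity analysis. The text gives no support for that, and the exact match to a plain t-test total speaks against it. The adequacy statement in the same section is made against this figure. The section Strengths and limitations also presents power to detect a 5% change as a distinguishing feature of the study.

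**Working it through.** **Inputs** (all from Required sample size)

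- Difference: 0.05 × 5 = 0.25 contacts
- Standard deviation: 6
- Two-sided significance level 0.05: z = 1.959964
- Power 90%: z = 1.281552
- Equal group sizes, no stated inflation

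**Step 1: normal approximation**

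n per group = 2 × (1.959964 + 1.281552)² × (6/0.25)² = 2 × 10.5074 × 576 ≈ 12,104.6, so 12,105 per group and 24,210 in total.

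**Step 2: two-sample t-test (noncentral t)**

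| n per group | Power |
|---|---|
| 12,105 | 0.89999 |
| 12,106 | 0.90001 |

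The requirement is 12,106 per group. The total is 2 × 12,106 = 24,212, which is the printed number to the patient.

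**Step 3: the printed figure taken literally**

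With 24,212 in each group the standard error is 6 × √(2/24,212) = 0.05453. Then 0.25/0.05453 = 4.584, and 4.584 − 1.960 = 2.624, so power is 99.6%. For 24,212 per group to be the 90% requirement, the difference would have to be about 0.177 contacts (3.5% of 5) or the standard deviation about 8.49. The article states neither.

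**Step 4: other ways to reach 24,212 per group**

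| Variant | n per group |
|---|---|
| One-sided test, 90% power | 9,866 |
| 80% power | 9,042 |
| 95% power | 14,970 |
| 99% power | 21,166 |
| One-sample test | 6,052 |
| Dilution by the Table 1 uptake difference | 21,725 |
| 3:1 allocation | 24,210 and 8,070 |

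For the dilution row, uptake differs by 67,770/84,931 − 5,420/105,250 = 0.798 − 0.051 = 0.746, and 12,105/0.746² gives 21,725 with the unrounded difference. The 3:1 split comes within 2 patients in its larger arm, but its smaller arm does not fit a figure said to apply to each group. No variant tried gives 24,212 in each group.

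**Step 5: why 12,106 is not the requirement for the planned analysis**

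The planned estimate is a ratio: the jump in outcome at age 75 divided by the jump in treatment receipt. The article does not say whether the 5% is the change across everyone near the threshold or the change among compliers, so both readings are shown.

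| Reading of the 5% | Difference at the threshold | Power at 12,106 per group | Power at 24,212 per group |
|---|---|---|---|
| Change across all patients | 0.25 | 90% | 99.6% |
| Change among compliers, uptake difference about 0.75 | 0.25 × 0.75 = 0.1875 | 68% | 93% |

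Neither row allows for extrapolating the polynomials to age 75 with patients born in 1939 excluded, or for any clustering by practice.

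**The case against.** **The cause is inferred.** The article does not say that 24,212 is a total. An unstated multiplier of exactly 2 applied to 12,106 would give the same number, and a fuller protocol or a cited source might contain one. This stands as a limit on wording: the figure appears to be mislabelled, and that is not proved. It does not remove the discrepancy, because the printed sentence does not follow from the inputs printed with it.

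**The uptake check is only one candidate.** The 0.746 compares two five-year age bands in preliminary data to which not all exclusions had been applied, so it is not the jump at age 75. Fuzziness is also not the only source of inflation in this design. That is fair. Failing to reach 24,212 by that route does not exclude every other factor; it shows only that the obvious one does not explain the figure.

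**The error does no harm to the study.** It overstates the simple requirement. Nothing is recruited, because the study takes eligible patients from existing records in about 200 practices. The smaller Table 1 count would have to fall to 24,212/84,931 = 28.5% of its size before even the printed figure was missed. This stands, and it limits the importance of the point.

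**Two stronger readings are tempting.** A reader might infer that the adequacy claim collapses. The documents do not support that, since a smaller requirement is easier to meet and the section already says that power depends on the bandwidth. A reader might instead infer that half the patients would do. Step 5 shows why that does not follow for the planned estimate.

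**Conclusion.** The per-group figure is wrong as written. On the stated inputs the requirement is 12,106 in each group and 24,212 in total, so the printed per-group size is too large by a factor of 2.00. A total labelled as a group size is the very likely explanation, because the match is exact and no inflation is stated.

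This rests on equal groups and a two-sided two-sample t-test, which is what the stated inputs describe. It is a correction that should be made to a stated figure. It is not a threat to feasibility, and it does not by itself undermine any planned estimate or test. Neither 12,106 nor 24,212 per group has been shown to be the requirement for the fuzzy regression discontinuity estimate. The 68% and 93% in the working rest on the assumptions that the 5% is a complier effect and that uptake differs by about 0.75.

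**What to change.** Reword the result in Required sample size along these lines: 24,212 patients in total (12,106 in each group) for an unadjusted two-group comparison at 90% power and a two-sided significance level of 0.05. If a multiplier of 2 was intended, keep the per-group figure and state the factor and its basis.

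In either case, add a sentence saying that this is not the requirement for the fuzzy regression discontinuity estimate. That estimate needs more, because of dilution by incomplete uptake, extrapolation to age 75 and any clustering by practice. State also whether the 5% refers to all patients near the threshold or to compliers. The figure 12,106 should not be printed alone as sufficient.

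The cost is two or three sentences, with no change to data, conduct or analysis.
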